### Who will take informed consent? {26a}

Written informed consent to enter and be randomised into the trial must be obtained from participants by an investigator (a doctor or a qualified research nurse), after explanation of the aims, methods, benefits, and potential hazards of the trial and before any trial-specific procedures are performed or any samples are taken for the trial.

### Additional consent provisions for collection and use of participant data and biological specimens {26b}

Consent provisions for collection and use of participant data and biological specimens are accounted for in the informed consent form approved by the National Committee of Scientific Investigation (IRB00003566) and the Mexican Regulator COFEPRIS.

## Interventions

### Explanation for the choice of comparators {6b}

#### Combination of favipiravir and nitazoxanide

Favipiravir and nitazoxanide have different mechanisms of action so given together are likely to act at least additively.

The preliminary results seen for favipiravir, and the promising in vitro activity of nitazoxanide, urgently need to be confirmed (or refuted) in a well-conducted, placebo-controlled trial. Therefore, there is a strong rationale for choosing to trial early oral antiviral therapy with favipiravir and to investigate its combination with nitazoxanide.

### Intervention description {11a}

Favipiravir 200 mg tablets will be provided free of charge by Strides Pharma Science Limited.

On day 1, 9 tablets (1800 mg) will be taken twice separated by at least 6 h (e.g. if the first dose is at 5 pm, the second dose should be at 11 pm), followed by 2 tablets (400 mg) four (4) times daily from day 2 to day 7.

Nitazoxanide tablets as well as nitazoxanide placebo tablets will be sourced free of charge by Siegfried Rhein, S.A de C.V.

On day 1, 2 tablets (1000 mg) will be taken twice separated by at least 6 h (e.g. if the first dose is at 5 pm, the second dose should be at 11 pm), followed by 1 tablet (500 mg) four (4) times daily from Day 2 to Day 7.

Treatment dosing regimen is summarised in Table 1 below:

**Table 1 Tab1:** Treatment dosing regimen

Arm	Total daily dosage	Regimen	Total No of tablets daily
**FAVI active + nitazoxanide active**	**Day 1:** FAVI = **3600mg**	**FAVI**: 1st dose: 1800mg (9 tablets) 2nd dose: 1800mg (9 tablets)	**Day 1:** FAVI = 18 tablets
**OR**			
**FAVI active + nitazoxanide placebo**	**PLUS**	**PLUS**	**PLUS**
	NITA = **1000 mg**	**LPV/r:** 1st dose: 1000mg (2 tablets) 2nd dose: 1000mg (2 tablets)	NITA = 4 tablets
	**Day 2 to day 7:** FAVI = **1600mg**	**FAVI**: 1st dose: 400mg (2 tablets) 2nd dose: 400mg (2 tablets) 3rd dose: 400mg (2 tablets) 4th dose: 400mg (2 tablets)	**Day 2 to Day 7:** FAVI = 8 tablets
	**PLUS**	**PLUS**	**PLUS**
	NITA = 5**00mg**	**NITA:** 1st dose: 500mg (1 tablet) 2nd dose: 500mg (1 tablet) 3rd dose: 500mg (1 tablet) 4th dose: 500mg (1 tablet)	NITA = 4 tablets

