## Discussion

Two recent pre-print papers [9, 10] on the viral dynamics of SARS-CoV-2, the cause of COVID-19, provide simulations to show that viral load peaks around 3 days after symptom onset and that antiviral therapy started later than day 4 may have limited benefit. Furthermore, late antiviral therapy, once viral loads are high, risks selection for drug resistance. Therefore, there are strong grounds to believe that if antivirals are to have a place in the treatment of SARS-CoV-2, they should be given early and, if possible, within the first 7 days of symptom onset.

Both recent SARS-CoV-2 modelling papers [9, 10] suggest that drugs need to provide a minimum of 65% inhibition of viral replication, with this percentage increasing to 90% or more if therapy is initiated late, meaning a combination therapy may improve the chances of achieving sufficient viral inhibition.

Favipiravir is orally administered and well absorbed with close to 100% bioavailability [11] . The drug is metabolized to a ribosyl triphosphate form which specifically inhibits the RNA-dependent RNA polymerase without affecting host RNA and DNA polymerases, thereby rendering it a specific inhibitor of viral RNA synthesis. The highest dose used in Phase II trials, for which safety is established, and hence proposed in this trial is 1800 mg twice daily on day 1 followed by 800 mg twice daily.

Favipiravir has been used clinically in several viral infections and in some cases, the drug has been observed to induce viral mutagenesis [12]. Occasional asymptomatic elevation of liver aminotransferase levels was observed, but no serious adverse events related to the drug. Importantly, animal studies have indicated potential teratogenicity and the drug is distributed in sperm: therefore, a negative pregnancy test for all women of child-bearing potential will be required and participants instructed to use adequate contraception for the duration of the treatment and 7 days afterward [13].

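### Table 1's nitazoxanide daily totals (1000 mg, then 500 mg) contradict its own regimen and tablet counts, which imply 2000 mg on every treatment day

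*Protocol article*

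**What the plan says.** The running text of the Intervention description {11a} sets the nitazoxanide regimen in two parts. For the first day: "On day 1, 2 tablets (1000 mg) will be taken twice separated by at least 6 h". After that: "followed by 1 tablet (500 mg) four (4) times daily from Day 2 to Day 7".

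Table 1, offered there as a summary of the regimen, has three columns that bear on dose:

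- **Dose total.** The column is headed "Total daily dosage". Its nitazoxanide entries are 1000 mg for Day 1 and 500 mg for Days 2 to 7. Its favipiravir entries are 3600 mg and 1600 mg.
- **Regimen.** The Day 1 nitazoxanide cell reads "LPV/r: 1st dose: 1000mg (2 tablets) 2nd dose: 1000mg (2 tablets"), and the cell for Days 2 to 7 reads "NITA: 1st dose: 500mg (1 tablet) 2nd dose: 500mg (1 tablet) 3rd dose: 500mg (1 tablet) 4th dose: 500mg (1 tablet").
- **Tablets per day.** Both periods show "NITA = 4 tablets".

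For favipiravir, {11a} and Table 1 give 1800 mg twice on Day 1 and 400 mg four times daily from Day 2 to Day 7. The Discussion gives the schedule proposed for this trial, on grounds of established safety, as "1800 mg twice daily on day 1 followed by 800 mg twice daily".

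**The concern.** A reader who takes the daily nitazoxanide dose from the total column gets a different figure from one who multiplies out the regimen or counts the tablets, and both are reading the same row. The Day 1 nitazoxanide cell also carries an abbreviation for lopinavir plus ritonavir (listed under Abbreviations with two letters transposed), which is not a study drug in either arm. The Discussion's safety rationale for favipiravir then describes a dosing frequency that the trial does not specify.

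What is at stake is clarity about the intended dose. Several parts of the protocol rely on it: the tablet counts under {11c}, the overdose trigger for unblinding under {17b}, and the dosing history for the pharmacometric model under {20b}. The article is also the route by which the full protocol is to be made public (Reproducible Research). It appeared on 22 July 2022, while recruitment was expected to run to 30 August 2022 (Trial status).

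**Working it through.** **Inputs.** All come from {11a} and Table 1 unless stated.

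- Nitazoxanide tablet strength: 500 mg, from 1 tablet being given as 500 mg and 2 tablets as 1000 mg.
- Favipiravir tablet strength: 200 mg.
- Doses per day, tablets per dose and tablets per day: as set out in the text and the table.
- Discussion, favipiravir after Day 1: 800 mg twice daily.

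**Formulas.** Daily total = dose × doses per day. Cross-check: tablets per day × tablet strength.

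**Step 1: is the column a daily total?** Test it on favipiravir.

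- Day 1: 2 × 1800 = 3600 mg; 18 × 200 = 3600 mg; stated 3600 mg.
- Days 2 to 7: 4 × 400 = 1600 mg; 8 × 200 = 1600 mg; stated 1600 mg.

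Both stated figures are reproduced by both routes, so the column holds daily totals, as its heading says.

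**Step 2: nitazoxanide by the same rule.**

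| Period | Regimen | Tablets | Stated total | Ratio |
|---|---|---|---|---|
| Day 1 | 2 × 1000 = 2000 mg | 4 × 500 = 2000 mg | 1000 mg | 2000 / 1000 = 2 |
| Days 2 to 7 | 4 × 500 = 2000 mg | 4 × 500 = 2000 mg | 500 mg | 2000 / 500 = 4 |

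Neither stated total is reproduced. Each equals one single dose. A per-dose reading does not rescue the column, because the favipiravir cells would then be wrong.

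**Step 3: over the seven-day course.**

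- By regimen: 2000 + 6 × 2000 = 14000 mg.
- By the stated totals: 1000 + 6 × 500 = 4000 mg.
- Ratio: 14000 / 4000 = 3.5.

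The 4000 mg figure appears nowhere in the document. It is only the sum of the disputed cells, so the ratio measures the size of the inconsistency.

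**Step 4: could this come from reading the table out of a PDF?** No. The running text gives the same nitazoxanide regimen as the regimen and tablet columns, so the conflict does not depend on table layout.

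**Step 5: favipiravir, {11a} against the Discussion.**

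- Day 1: 2 × 1800 mg in both.
- After Day 1: 4 × 400 = 1600 mg in {11a}; 2 × 800 = 1600 mg in the Discussion.

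The daily total is the same. Dose size and frequency differ.

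**The case against.** The strongest reply is that the regimen is not in doubt. The text, the regimen column and the tablet column agree on nitazoxanide, and only two cells stand apart. Staff who follow doses and tablets would act consistently. The table only summarises the text, and dispensing runs through coded kits, a prescription bearing the kit code and separate participant instructions ({16a}, {16c} and the Screening/baseline visit), none of which is shown. This stands. A reader might infer that over- or under-dosing cannot be judged at all, or that participants received the wrong dose; the document supports neither.

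A reader might also infer that adherence data and the pharmacokinetic model are corrupted. That does not follow. Adherence rests on diaries and tablet counts ({11c}), Day 7 dose times are recorded to the minute ({33}), and the model's dosing history comes from the clinical database ({20b}). No section feeds the table's milligram totals into a dataset. What remains is that someone coding the intended dose from the total column could be misled.

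The LPV/r label can fairly be called editorial: the cell sits in the nitazoxanide row and its contents match the nitazoxanide text. The favipiravir difference is mild, since Day 1 and the daily total agree. It is still not empty, because the Discussion sentence claims to state this trial's own schedule, and the Day 7 samples are timed to the dose.

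None of this removes the contradiction in the nitazoxanide totals.

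**Conclusion.** The contradiction is established from {11a} and Table 1 alone. The stated nitazoxanide daily totals differ from what the text, the regimen column and the tablet count each imply, by a factor of 2 on Day 1 and 4 on Days 2 to 7. The only derived input is the 500 mg tablet strength, which the text itself fixes.

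The stray drug label and the favipiravir frequency difference are real but minor.

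The consequence is an avoidable safety ambiguity in a dosing table, with some risk of misleading anyone who takes the intended dose from the total column. It is not evidence of misdosing or of damaged data, and the 3.5-fold course ratio is not an estimate of exposure risk. That three entries agree and one does not shows where the conflict lies. It does not settle which dose is right, and no view is taken on that here.

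**What to change.** The sponsor should reconcile the following so that they state one regimen:

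- the total-dosage column of Table 1 for nitazoxanide;
- the regimen and tablet columns of Table 1;
- the LPV/r label in the Day 1 cell;
- the running text of {11a};
- the Discussion sentence on the favipiravir schedule.

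The sponsor should then confirm that kit labels, participant instructions and the dosing records used for adherence and pharmacometric work match the reconciled version. Which figure and which schedule are right is for the sponsor to determine.

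The cost is small: a published correction to one table and, depending on the outcome, to one sentence each in {11a} and the Discussion, plus a document check. The design, sample size and planned analyses are unaffected.

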### Criteria for discontinuing or modifying allocated interventions {11b}

In consenting to the trial, participants are consenting to trial treatments, trial follow-up and data collection. However, an individual participant may stop treatment early or be stopped early for any of the following reasons:Unacceptable treatment toxicity or adverse event.Inter-current illness that prevents further treatment.Any change in the participant’s condition that in the clinician’s opinion justifies the discontinuation of treatment.Participant no longer wants to continue taking the trial medications.

### Strategies to improve adherence to interventions {11c}

Every attempt to contact participants who do not adhere to the trial or who terminate participation prematurely will be made. This will include a telephone call on Day 5 from delegated members of the research team. Participants will complete diaries and tablet counts at the end of the intervention period. Reasons for non-adherence or non-retention will be documented.

### Relevant concomitant care permitted or prohibited during the trial {11d}

All medications (except those that are contraindicated according to the nitazoxanide SPC and favipiravir IB) which the trial investigator responsible for the participant’s care feels are clinically appropriate, are permitted in the trial.

If a participant is hospitalised during the trial period they will be encouraged where possible to continue taking trial medication, taking nose swab samples, and recording temperature, but any urgent medical treatment required will be permitted.

### Provisions for post-trial care {30}

No arrangements will be in place for trial treatment after the planned treatment phase. Participants will be cared for as per standard IMSS care should they require further treatment or hospitalisation for their COVID-19 symptoms. This will be made clear in the informed consent form.

### Outcomes {12}

The primary outcome is the upper respiratory tract viral load at day 5.

Method of measurement: quantitative polymerase chain reaction (PCR) performed on nose swab samples.

The secondary outcomes are the following:Percentage of participants with undetectable upper respiratory tract viral load after 5 days of therapy.

Method of measurement: quantitative polymerase chain reaction (PCR) performed on nose swab samples.Proportion of participants with undetectable stool viral load after 7 days of therapy and 14 days post-randomisation.

Method of measurement: PCR performed on stool samples.Rate of decrease in upper respiratory tract viral load during 7 days of therapy.

Method of measurement: PCR performed on daily nose swab samples.Duration of fever following commencement of medication.

Methods of measurement: daily body temperature records between Day 1 and Day 7 post- randomization.Proportion of participants with hepatotoxicity after 7 days of therapy and 14 days post-randomisation.

Method of measurement: standard diagnostic laboratory assays for liver transaminases, alkaline phosphatase and bilirubin.Proportion of participants with other medication-related toxicity after 7 days of therapy and 14 days post-randomisation.

Methods of measurement: determination of medication-related adverse events by investigators.Proportion of participants admitted to hospital with COVID-19-related illness.

Methods of measurement: participant self-report, review of hospital records and discharge summaries.Proportion of participants admitted to ICU with COVID-19-related illness.

Methods of measurement: participant self-report, review of hospital records and discharge summaries.Proportion of participants who have died with COVID-19-related illness.

Methods of measurement: next of kin report, review of hospital records and discharge summaries.Pharmacokinetic and pharmacodynamic analysis of favipiravir and tizoxanide.

Method of measurement: assay of favipiravir and tizoxanide levels in plasma at day 7 of therapy. All participants from each arm will provide a pre-dose trough sample and a post-dose (30 to 60 min) sample on Day 7 of therapy. A nonlinear mixed effects model will be fitted jointly to favipiravir and tizoxanide pharmacokinetic and viral load (pharmacodynamic) data.

The model will estimate the following primary PK parameters:

PK: Clearance (CL), volume of distribution (V), absorption rate constant (Ka) from which the following secondary parameters will be derived:Maximum concentration (Cmax),Time to maximum concentration (Tmax), elimination rate constant (Ke),Area under the curve extrapolated to infinity (AUC (0-inf)).The model will also estimate the following pharmacodynamic parameters: Rate of viral load decline (delta), andMaximum increase in viral load under drug treatment (Emax), Concentration to achieve half the maximum possible effect (EC50).Exploratory: proportion of participants with deleterious or resistance-conferring mutations in SARS-CoV-2.

Method of measurement: deep sequencing of virus and bioinformatic analysis.

### Participant timeline {13}

The participant timeline is shown in Table 2.

**Table 2 Tab2:**
[figure not shown]
Participant timeline

### Sample size {14}

We have conducted extensive power calculation and power simulation exercises for the proposed design [6]. In the proposed design 120 participants (108 evaluable participants, which implies a 10% allowance for attrition and other methodological challenges) will be recruited, so that half of the participants receive both favipiravir/nitazoxanide treatment, and the other half receive favipiravir/nitazoxanide placebo treatment. We hypothesised that around a 1 log10 difference in viral load by day 5 would be clinically significant.

### Recruitment {15}

The trial will be advertised at each site and the participant identification centre and health workers provided with the trial team’s contact details. Occupational Health teams at each participating centre will be provided with the trial information which they can provide to health workers who consult them. Potential participants will also be approached after research on databases. 120 participants will be recruited in total (60 participants in each arm) over an overall period of 6 months.

Should recruitment targets be slower than anticipated other clinics, hospitals, and diagnostic laboratories in México City and its suburban area will be approached to enroll participants, which will be done centrally by the trial team in any case.

Recruitment will be monitored regularly to identify any barriers to recruitment. Reporting will be conducted on a regular basis over the trial set-up and recruitment period to the Trial Management Group (TMG), and trial oversight committees. Remedial action will be put in place as soon as any concerns have been raised.

## Assignment of interventions: allocation

### Sequence generation {16a}

Participants will be randomised 1:1 using a stratification process, with the following factors: study site, age (≤ 55 vs > 55 years old), gender, obesity (BMI <30 vs ≥30), symptomatic or asymptomatic, current smoking status (Yes = current smoker, No = ex-smoker, never smoker), and the presence or absence of comorbidity (defined as diabetes, hypertension, ischaemic heart disease (including previous myocardial infarction), other heart diseases (arrhythmia and valvular heart disease), asthma, COPD, other chronic respiratory diseases) and, if the participant has or not been vaccinated. These data will be collected at the pre-screening telephone contact and will be used for the purposes of registration and IMP kit pre-allocation.

Considering the importance of starting therapy immediately upon entering this trial, IMP kit codes will be pre-allocated to the participants ahead of the screening/baseline visit on day 1.

The Trial Pharmacologist at CINVESTAV will generate a sequence of unique identifiers for every active/placebo IMP kit. A copy of the sequence will be held securely at UCL and at CINVESTAV.

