**Methods:**

Trial design: Phase IIA randomised, double-blind, 2 × 2 design, placebo-controlled, interventional trial.

Randomisation: Participants will be randomised 1:1 by stratification, with the following factors: gender, obesity, symptomatic or asymptomatic, current smoking status presence or absence of comorbidity, and if the participant has or has not been vaccinated. Blinding: Participants and investigators will both be blinded to treatment allocation (double-blind).

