### Implementation {16c}

Randomisation will be done through the RedCap database using stratification in which patients will first be grouped into strata according to the following factors: age, gender, obesity, symptomatic or asymptomatic, smoking, and vaccination status. Within each stratum, patients will be randomly assigned to one of the two arms of the study.

Following the pre-screening telephone contact before screening/baseline visit, the clinical investigator or delegate will enter the participant’s initials, and all the factors stated above. and confirm participant eligibility on the RedCap secure online system and allocate the appropriate PIN to the patient.

Delegated staff at participating sites will be provided with a secure login to the RedCap website, according to their role in the trial. The randomisation result will be shown directly online as a unique IMP kit code, with an email confirmation sent to the user and to the trial team. The investigator will provide details of the allocated unique kit code assigned to the participant on the prescription. Delegated staff will collect the allocated IMP kit from pharmacy on behalf of the participant ahead of the screening/baseline visit.

Randomisation will be considered complete after the participant has signed the consent form and ingests their first dose of trial medication during screening/baseline visit. Participants who withdraw before taking their first dose will be considered withdrawn prior to randomization.

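### The stratification factor lists disagree and, fully crossed, give 64 to 128 or more strata for 120 participants, so the scheme cannot ensure the balance or the 60/60 split it aims for

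*Protocol article*

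**What the plan says.** Three places in the protocol article give the stratification factors.

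- **Sequence generation {16a}:** "study site, age (≤ 55 vs > 55 years old), gender, obesity (BMI <30 vs ≥30), symptomatic or asymptomatic, current smoking status", followed by comorbidity and vaccination. That is site plus seven two-level factors.
- **Implementation {16c}:** "age, gender, obesity, symptomatic or asymptomatic, smoking, and vaccination status". That is six two-level factors, without site or comorbidity.
- **Abstract, Methods:** "gender, obesity, symptomatic or asymptomatic, current smoking status presence or absence of comorbidity", followed by vaccination. That is six two-level factors, without site or age.

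Implementation {16c} also fixes the mechanism. Patients are first grouped into strata, and then: "Within each stratum, patients will be randomly assigned to one of the two arms of the study". Minimisation is not mentioned anywhere. Recruitment {15} plans "120 participants will be recruited in total (60 participants in each arm) over an overall period of 6 months". Study setting {9} names one hospital, while Recruitment {15} and Implementation {16c} speak of sites in the plural.

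**The concern.** There are two linked problems.

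First, {16a} and {16c} both set out to name the randomisation factors, and they disagree on comorbidity and site. A reader cannot tell which scheme produced the allocation, or which factors an analysis that respects the randomisation should include.

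Second, stratification balances the arms only when strata are large enough to fill blocks. Crossing six or seven factors in a trial of 120 leaves many strata with one participant, whose assignment is in effect a coin toss. What is at stake is chance imbalance on factors the investigators chose to control, such as vaccination, symptom status and age, together with unequal arms.

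**Working it through.** **The plan's own figure.** Sample size {14} gives "108 evaluable participants, which implies a 10% allowance for attrition and other methodological challenges". 108 / (1 − 0.10) = 120, and 120 / 2 = 60 per arm. This reproduces exactly.

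**Number of strata** = 2^(two-level factors) × sites.

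- {16a}: 2^7 = 128 with one site, or 120/128 = 0.94 participants per stratum. Two sites give 256 strata and three give 384.
- {16c} and the abstract: 2^6 = 64 each, or 120/64 = 1.9 per stratum.

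**Benchmark: simple randomisation of 120.** This is also what unblocked random assignment within strata amounts to. With D the difference in arm sizes:

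- SD(D) = √120 = 10.95
- P(exactly 60/60) = C(120,60)/2^120 = 7.3%
- P(|D| ≥ 10) = 41%

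**Permuted blocks within strata, by simulation.** The article gives neither prevalences nor block size, so both are assumed and varied. The main uneven set is: over 55, 20%; male, 50%; obese, 35%; symptomatic, 90%; smoker, 15%; comorbidity, 30%; vaccinated, 80%. One site is assumed, with no places in a stratum lost to withdrawals before the first dose.

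| Scheme | Block size | SD(D) | P(difference of 10 or more) |
|---|---|---|---|
| Simple randomisation | none | 10.95 | 41% |
| Seven factors, uneven | 4 | 6.6 | 17–18% |
| Six factors of {16c}, uneven | 2 / 4 / 6 | about 4.2 / 5.5 / 6.1 | about 3 / 10 / 13% |
| Seven factors, all at 50% | 2 / 4 / 6 | 7.5 / 9.2 / 9.6 | 22 / 32 / 36% |
| Six factors, all at 50% | 2 / 4 / 6 | 5.6 / 7.6 / 8.6 | 10 / 24 / 30% |
| Two factors | 4 | about 1.8 | – |

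With seven factors and uneven prevalences, about 43 strata are occupied, about 21 of them by one person, and with blocks of 4 about half of participants fall in completed blocks. With all seven factors at 50%, about 78 strata are occupied, about 47 of them by one person. A second uneven set (obese 40%, one in five in the smaller symptom category, the rest unchanged) gives SDs of 5.5, 6.9 and 7.7 on seven factors for blocks of 2, 4 and 6.

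**Balance on individual factors** (six factors, blocks of 4, main uneven set). The measure is the between-arm difference in the number with the characteristic, allowing for arm size. Under simple randomisation its SD is √(120·p·(1−p)).

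- Vaccination: √(120 × 0.8 × 0.2) = 4.4 falls to 2.7.
- Age: √(120 × 0.2 × 0.8) = 4.4 falls to 2.7.
- Symptoms: √(120 × 0.9 × 0.1) = 3.3 falls to 2.6.

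**Efficiency lost through unequal arms.** Relative efficiency = (4/N)/(1/n1 + 1/n2) = 1 − (D/N)². With N = 108:

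- D = 10: 1 − (10/108)² = 0.991, a loss of about 1%.
- D = 20: 1 − (20/108)² = 0.966, a loss of about 3.4%.

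**The case against.** A reader might infer that so fine a stratification does little more than simple randomisation and cannot deliver 60/60. The figures do not support that. With uneven prevalences, seven factors and blocks of 4, the variance of the arm difference falls by 1 − (6.6/10.95)² = 64%. The six-factor list does better, and balance improves on each of the three factors examined. Only the case with every factor at 50% comes near simple randomisation, and that is implausible for symptom status in a COVID-19 treatment trial. Sixty per arm also reads as a recruitment target that chance may meet, not as a guarantee.

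It is equally tempting to say that no blocks are used, so stratification has no effect. The article is silent on blocks, and a condensed article may leave block size to the full protocol. That silence is no finding.

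A third inference is that the analysis cannot reflect the randomisation. {16a} says the listed factors are collected at the pre-screening call, so any of them can be adjusted for, and the covariate set may be in an analysis plan not shown.

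An abstract may also shorten a list, and omitting site matters little if there is one site. Unequal arms do not bias the comparison. All of this stands. It leaves untouched the conflict over comorbidity between {16a} and {16c}, and the one to two participants per stratum on every version of the list.

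**Conclusion.** The point holds as a design weakness and an inconsistency to correct. It does not threaten the validity of the comparison. The strata count follows from the text: 128 or more under {16a}, 64 under {16c} or the abstract, for 120 participants. The scheme therefore cannot ensure balance or equal arms. It still improves on simple randomisation if small blocks are used. The SD of the arm difference is then about 4 to 7 under the main uneven prevalences (up to 7.7 in the second set), and up to about 9 to 10 if every factor is at 50%, against 11. These SDs rest on assumed prevalences, blocks of 2 to 6 and one site; more sites would make the strata sparser. The efficiency loss is about 1% at a difference of 10. The main harms are avoidable chance imbalance on factors chosen for control and an unclear record of how participants were randomised.

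**What to change.** 1. Establish from the RedCap configuration which factors were used, and state that one list in the abstract, {16a} and {16c}, including whether site has more than one level.
2. For any participants still to be randomised, either cross only two or three prognostic factors (for example vaccination and symptom status) in small permuted blocks, or use minimisation with a random element. Report the change and when it took effect.
3. In the primary and secondary models, adjust for the factors actually used in randomisation and for the remaining listed factors, which are already collected. Logistic models for rare outcomes such as ICU admission or death may not support the full set, so a reduced set should be named in advance for those.

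The cost is a short amendment and a new allocation table or minimisation routine, with a mixed allocation scheme to report. Trial status expects recruitment to end by August 30, 2022, and the article appeared on July 22, 2022, so step 2 may reach few participants. Steps 1 and 3 then carry most of the benefit and need no change to trial conduct.
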